## Abstract

**Background:**

Laboratory studies indicate that chemicals in fruits and vegetables have anti-carcinogenic and anti-inflammatory activities that can lower breast cancer risk. However, epidemiologic studies of the association between fruit and vegetable intake and breast cancer risk have produced mixed results. Measurement error, confounding, and an emphasis on diet in later adulthood may contribute to weak associations. This paper describes a randomized controlled diet intervention trial in breastfeeding women to examine the effect of high fruit and vegetable intake on breast cancer risk factors, including weight, DNA methylation and inflammatory markers.

**Methods:**

Eligible breastfeeding women who reside within a 35-mile radius of Amherst, MA are enrolled at five to six weeks postpartum and randomly assigned to a Fruit and Vegetable Intervention Arm (target n = 200) or to a USDA MyPlate Control Arm (target n = 200). The Fruit and Vegetable Intervention group receives weekly telephone or video-based counseling to encourage intake of at least eight to ten daily servings of fruits and vegetables and a weekly delivery of a supplemental box of fruits and vegetables for 20 weeks, and less intensive counseling for up to one year. Breastmilk and infant fecal specimens are collected at baseline, 10 and 20 weeks. Anthropometric measurements are obtained at these timepoints and at the 1-year follow-up. The primary outcomes are change in DNA methylation in breast epithelial cells and change in inflammatory markers in breastmilk from randomization to 20 weeks; and change in weight, waist circumference, and fruit and vegetable intake for the period from randomization to 20 weeks and 1 year.

**Discussion:**

This 1-year randomized diet intervention trial in breastfeeding women will assess whether intake of at least eight to ten daily servings of fruits and vegetables per day improves biomarkers of breast cancer risk directly in the breast (i.e., DNA methylation and inflammatory markers) and helps women maintain a healthy weight.

*Trial registration*: ClinicalTrials.gov Identifier: NCT04374747. Registered May 5, 2020. https://www.clinicaltrials.gov/ct2/show/NCT04374747.

## Background

Compounds in fruits and vegetables have anti-carcinogenic and anti-inflammatory activity that may lower breast cancer risk [1]. However, studies of the association between fruit and vegetable intake and breast cancer risk have produced mixed results. The 2017 American Institute for Cancer Research report concluded that there is some evidence that non-starchy vegetables and carotenoid-rich foods reduce risk [1]. Higher vegetable intake may be more strongly associated with a reduction in estrogen receptor (ER)-negative breast cancer [2]. Most prior studies have been observational in design with a focus on diet in later adulthood. Therefore, we will address a significant gap in the literature by conducting a randomized trial in young women to assess the effect of consuming up to 8 to 10 daily servings of fruits and vegetables on biomarkers of breast cancer risk in the breast microenvironment and helps women maintain a healthy weight. We hypothesize that high fruit and vegetable intake in this population will favorably impact DNA methylation patterns and the inflammatory profile in the breast.

Global DNA hypomethylation and hypermethylation of tumor suppressor genes are key early events in breast carcinogenesis [3]. Aberrant DNA methylation patterns in breast cells are highly promising molecular biomarkers of breast cancer risk [4]. Chronic inflammation may also be involved in breast cancer development and progression. Many prospective studies have examined the relation between higher blood levels of c-reactive protein (CRP), and risk of breast cancer, and the overall findings indicate a modest positive association [5]. While the weight of evidence supports a role of inflammation in the development of breast cancer, the weak associations in epidemiologic studies have been attributed to the focus on circulating inflammatory markers. There is considerable evidence indicating that serum is not adequate surrogate tissue for understanding local inflammatory activity in the breast and breast cancer risk [6].

Our intervention study population is breastfeeding women because the risk of breast cancer is increased for many years after childbirth [7]. In addition, a dietary intervention to reduce breast cancer may be more effective in younger than in older women. Finally, breast milk provides access to the breast to study DNA methylation and inflammation.

Although DNA methylation is considered stable, environmental exposures including diet, can alter methylation patterns [8–10]. Most studies of diet and epigenetics have focused on foods that supply nutrients (I.e., folic acid and B vitamins) for the one-carbon metabolic pathway because of the pathway’s role in supplying methyl groups needed in the DNA methylation reaction [10]. Direct dietary supplementation with foods aimed at enriching the methyl pool is just one way diet can alter DNA methylation. Compounds in fruits and vegetables (e.g., polyphenols, Vitamin C, lycopene, isothiocyanates) may also decrease methylation by inhibiting DNA methyltransferases, or by acting as cofactor to demethylation enzymes [9, 10]. Several prior studies have shown an intriguing association between diets rich in fruits and vegetables and DNA methylation patterns. For example, a prudent diet high in fruits and vegetables was associated with a lower prevalence of global hypomethylation measured in white blood cell (WBC) DNA than a western diet [11]. In another study, a four-week intervention in which participants were randomized to one of three diet groups (balanced fruits and vegetables, a diet rich in flavonoids and isothiocyanates, or a diet supplemented with flavonoids) showed that all three interventions resulted in a small but reproducible decrease in hypomethylation of WBC DNA as compared to pre-intervention levels [12]. Another study reported that diets containing 300 g of vegetables and legumes plus hazelnut oil for eight weeks resulted in a favorable reduction in methylation of *ADRB3* in blood of overweight and obese women without weight loss [13]. Intriguingly, DNA methylation was also altered in nipple aspirate cells of women participating in an intervention study with isoflavones after one month [14]. In summary, DNA methylation is a key event in carcinogenesis and diet, particularly fruit and vegetable intake, may be an effective way to shift DNA methylation patterns to lower breast cancer risk, yet the effect of a diet rich in fruits and vegetables has not been assessed directly in breast tissue.

The role of intake of fruits and vegetables in reducing inflammation in the breast is unknown. Several dietary intervention studies (ranging from 3 months to 2 years in length) have suggested that a dietary pattern high in fruits and vegetables is associated with increased blood levels of adiponectin, and lower blood levels of IL-6, and CRP [15]. For example, Watzl and colleagues reported a significant decrease in CRP levels after participants consumed 8 daily servings of vegetables for 4 weeks [16]. However, understanding the potential effects of a diet rich in fruits and vegetables on breast tissue levels of inflammatory markers is more relevant to breast cancer susceptibility.

Therefore, we are conducting a 1-year randomized diet intervention trial (parallel design, 1:1 allocation, superiority framework) in breastfeeding women to assess the extent to which intake of at least eight to ten daily servings of fruits and vegetables improves biomarkers of breast cancer risk (i.e., DNA methylation and inflammatory markers) and helps women maintain a healthy weight.

### Aims

Specific aims for mothers are: (1) to determine the extent to which a diet intervention high in fruits and vegetables, compared to a control diet alters breast epithelial cell DNA methylation, breastmilk inflammatory profiles and maternal weight and waist circumference at 10 and 20 weeks; and (2) at 20 weeks and the 1-year interval, determine the extent to which randomization to the 1-year diet intervention, compared to the control diet, helps mothers increase fruit and vegetable consumption and maintain a healthy weight and body fat distribution.

## Methods

### Overview

Participants for the New Moms Wellness Study will be recruited from both pregnant women who plan to breastfeed and recently postpartum breastfeeding women who reside within a 35-mile radius of Amherst, Massachusetts. Eligible women will be enrolled at five to six weeks postpartum and randomly assigned to a Fruit and Vegetable Intervention Arm (target n = 200) or to Control Arm (target n = 200). The Fruit and Vegetable Intervention Arm will receive weekly telephone or video counseling and a weekly home delivery of supplemental fruits and vegetables for 20 weeks, and less intensive counseling for up to one year. All women will have access to a lactation counselor during the study. Remote study visits will occur at baseline, 10 weeks, 20 weeks and one year. Annual follow-up will continue for up to three years.

Data will be collected using REDCap hosted at University of Massachusetts Worcester [17, 18].

Although our original study design involved four home visits with in-person measurements (anthropometrics and skin carotenoid levels), the onset of the SARS-CoV-2 pandemic necessitated adopting a fully remote design as described below.

### Eligibility criteria

Eligible women will be women five to six weeks postpartum who are breastfeeding and over 18 years of age, who reside within 35 miles of Amherst MA or Worcester MA, and who have a National Cancer Institute Fruit and Vegetable Screener score indicating five or fewer servings of fruit and vegetables consumed per day over the past month [19]. Women with the following characteristics will be excluded: prior cancer in the past five years; a condition which may interfere with digestion and absorption of nutrients, body mass index < 18.5 kg/m^2^ or a personal history of diabetes (excluding gestational diabetes). An eligibility checklist will be administered at the time of first contact (up to 9 months prior to enrollment) and this requirement will be included as part of the informed consent process. The fruit and vegetable screener will not re-administered as we consider fruit and vegetable consumption to be relatively stable and most newly postpartum women do not consume more than five servings of fruits and vegetables per day.

### Recruitment

Potential study participants will primarily contact us though our website portal, having learned of the study through social media (including new mother groups, community listservs, and Facebook sponsored advertisements), print and electronic brochures at pediatric, midwifery, obstetric offices, birth classes, breastfeeding classes, Women Infant and Children’s (WIC) offices, community baby showers, and local businesses. Some participants will be recruited by a few practices or businesses that briefly describe the study to clients and will collect contact information from interested study participants that will then be shared with us for follow-up. All recruitment and study materials will be translated into Spanish.

### Randomization

All participants will provide written informed consent. Randomization will occur shortly after the baseline visit by study personnel. We will use block randomization (1:1 allocation) by self-reported body mass index (kg/m^2^) [18.5–24.9, 30+) and self-reported race/ethnicity (White non-Hispanic, White Hispanic, Black, Non-Hispanic or Black Hispanic, Other). The allocation sequence will be created by the biostatistician using computer-generated random numbers, and implementation will be through REDCap.

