#### Potential covariates and modifiers

We will collect detailed information at the baseline visit on reproductive history, hormone use, prior pregnancies and breastfeeding practices, tobacco use and vaping, marijuana use, alcohol intake, weight, breast health, multivitamin and supplement use during pregnancy, and family history of breast and ovarian cancer. We will also collect updated information on physical activity, breastfeeding and infant feeding practices, medication and supplement use, and breast health.

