#### Changes in inflammatory markers and methylation profiles comparing the intervention arm to control arm

To conserve power for the DNA methylation analysis, we will analyze approximately the most variable 300 K DNA methylation profiles. Each inflammatory and methylation marker will be analyzed in separate linear mixed effects models with a random intercept to account for the within subject correlation of the repeated measurements obtained at baseline and 20 weeks. Prior to analysis, each marker will be natural logarithm transformed to satisfy normality assumptions. Each linear mixed effects model will be of the form: E(Y_ij_) = β_0_ + β_1_ x T_ij_ + β_2_ x G_i_ + β_3_ x G_i_ x T_ij_, where Y_ij_ denotes the CpG or inflammatory marker measurement for subject *i* at visit *j*, T_ij_ is the time (post randomization) for subject *i* at visit *j* and G_i_ denotes the randomization group for subject *i*. The primary hypothesis test of interest is H_0_: β_3_ = 0, testing the interaction of randomization group with time, using a likelihood ratio test. As a secondary analysis, we will also consider a linear model in which the baseline CpG level is included as an additional covariate. Missing data imputation methods will be considered to confirm the robustness of the findings. Adjustment for multiple comparisons will be based on the False Discovery Rate (FDR) procedure of Benjamini and Yekutiel [31], which allows for correlation between CpG or inflammatory marker levels. Threshold for statistical significance will be based on the raw p value that controls the rate of false discoveries to be under 5%. The adjustment for multiple testing will be carried out separately for the set of 300,000 CpG measurements and the set of 12 inflammatory markers.

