#### Changes in maternal body weight and body fat distribution comparing the intervention arm to control arm at 20 weeks

Separate multivariate linear regression models will be fit to analyze the effect of randomization group on body weight or body fat distribution (waist circumference) at the end of intervention at 20 weeks. Body weight or waist circumference at 20 weeks will be considered as the outcome, with independent covariates including baseline weight or waist circumference, randomization group and other potential confounders. The distributions of body weight and waist circumference will be examined graphically and appropriate transformations (e.g., natural logarithm) will be considered. The statistical significance of the effect of randomization group on outcome will be assessed through a likelihood ratio test.

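### The printed BMI randomisation strata leave eligible women with BMI 25–29.9 without a stratum, and the weight, waist and intake models should name the stratification factors

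*Protocol article*

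**What the plan says.** All places are in the protocol article.

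- **Randomization.** Allocation is blocked ("We will use block randomization (1:1 allocation") and stratified "by self-reported body mass index (kg/m^2^) [18.5–24.9, 30+) and self-reported race/ethnicity". The race/ethnicity list is "White non-Hispanic, White Hispanic, Black, Non-Hispanic or Black Hispanic, Other", most naturally read as four categories. The biostatistician creates the sequence and REDCap implements it.
- **Eligibility criteria.** The only BMI rule is an exclusion: "body mass index < 18.5 kg/m^2^ or a personal history of diabetes (excluding gestational diabetes". There is no upper BMI limit.
- **Data analysis, weight and waist at 20 weeks.** A linear model with "independent covariates including baseline weight or waist circumference, randomization group and other potential confounders". The 1-year section reuses this form for intake, weight and waist.
- **Data analysis, markers and methylation.** The mixed model is written out as "E(Y_ij_) = β_0_ + β_1_ x T_ij_ + β_2_ x G_i_ + β_3_ x G_i_ x T_ij", with a random intercept and with baseline and 20-week values both as outcomes. The test is on β3.
- **Potential covariates and modifiers.** After the list of baseline data: "We will also collect updated information on physical activity, breastfeeding and infant feeding practices, medication and supplement use, and breast health".

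**The concern.** A stratified allocation rule has to place every eligible participant in exactly one cell. The printed rule does not, and the gap is in a factor closely tied to two primary outcomes, weight and waist. A reader cannot tell whether overweight women had their own stratum, were merged with another group or were allocated outside the strata, so the allocation cannot be reproduced from the article.

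Stratified allocation also has a consequence for analysis. It balances the arms on the strata and so reduces the true variance of the arm difference. A linear model that ignores the strata does not credit that reduction and reports a standard error that is too large. The models for weight, waist and intake name the baseline value and the arm, then leave the rest to an unnamed set of confounders. The strata may or may not be among them.

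**Working it through.** **1. Coverage of the BMI strata.** Inputs: the two printed intervals (Randomization) and the eligible range, BMI 18.5 or above (Eligibility criteria).

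| BMI | Eligible | Printed stratum |
|---|---|---|
| 18.5, 22, 24.9 | yes | 18.5–24.9 |
| 25, 27.5, 29.9 | yes | none |
| 30, 35 | yes | 30+ |

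As printed there are 2 × 4 = 8 cells. With a 25–29.9 category there are 3 × 4 = 12, and the eligible range is covered. The article does not give the share of women with BMI 25–29.9. If it were 25–33% (assumption), 400 × 0.25 = 100 to 400 × 0.33 = 132 women would belong to the unlisted category.

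**2. Cost of leaving the strata out of a linear model.** Let R² be the share of outcome variance that the strata explain beyond the baseline value. The article gives no figure, so a range is shown. Under stratified 1:1 allocation the true standard error is proportional to √(1 − R²), while the model without strata reports one proportional to 1.

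- Confidence interval width, omitted relative to included: 1/√(1 − R²). R² = 0.05 gives 1/√0.95 = 1.026; R² = 0.15 gives 1/√0.85 = 1.085.
- Actual two-sided type I error at nominal 0.05 with strata omitted: 2 × [1 − Φ(1.96/√(1 − R²))]. For R² = 0.10 this is 2 × [1 − Φ(2.066)] = 0.039; for R² = 0.20, 2 × [1 − Φ(2.191)] = 0.028.

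A simulation agrees. It used 400 women, 12 strata with assumed shares, permuted blocks of an assumed size 4, an assumed difference of 0.28 SD for power, and 4,000 runs per setting:

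| R² | Type I error, omitted | Type I error, included | Power, omitted | Power, included |
|---|---|---|---|---|
| 0 | 0.051 | 0.052 | 0.80 | 0.80 |
| 0.05 | 0.042 | 0.049 | 0.80 | 0.81 |
| 0.10 | 0.038 | 0.050 | 0.81 | 0.84 |
| 0.20 | 0.028 | 0.051 | 0.82 | 0.88 |
| 0.30 | 0.021 | 0.047 | 0.84 | 0.92 |

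Omission never inflates false positives. It costs little at R² near 0.05 and becomes material from about 0.10.

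**3. The marker mixed model.** Write woman i's two values with a stratum effect s_i: Y_i0 = β0 + β2G_i + s_i + u_i + e_i0 and Y_i1 = β0 + β1 + (β2 + β3)G_i + s_i + u_i + e_i1, with time coded 0 and 1. Subtracting gives Y_i1 − Y_i0 = β1 + β3G_i + (e_i1 − e_i0). The stratum effect cancels, along with the random intercept. With complete pairs, β3 is estimated from this change alone, so stratum main effects cannot alter it. In simulated data with 400 women and strong stratum effects, adding the strata left the β3 estimate unchanged to rounding error, with a standard error ratio of 1.000. With 20% of 20-week values missing, the ratio was 1.004.

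**The case against.** The strongest reply is that the gap is lost text and not a design fault. The opening square bracket and closing round bracket do not match, which is what a deleted middle category would leave behind, and the sequence actually used sits in REDCap, not in the article. This stands as an explanation. A reader might infer that the allocation list had no cell for these women, or that 100 or more were randomised outside the strata. Nothing in the article shows that. But the article chose to state the strata, and its statement conflicts with its own eligibility rule, so it needs correcting.

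A second reply is that a condensed article may leave the covariate list to the full protocol or SAP, and that the unnamed confounders could include the strata. This also stands. It cannot be said that no planned model contains them; their absence is explicit only in the marker model, where it does no harm. Baseline weight or waist will also already carry part of the BMI stratum, which lowers the R² that matters.

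A third stronger reading is that the plan adjusts for post-randomisation variables such as updated activity, breastfeeding or supplement use, which the diet may change. The covariates section says only that these data are collected. It does not say that they enter the outcome models, so bias from that source is a possibility to close off, not something the plan states.

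**Conclusion.** The conflict between the printed BMI strata and the eligibility criteria is certain on the text and holds whatever share of women is affected. Whether the allocation itself was affected is unknown.

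Naming the strata in the linear models for weight, waist and intake is a worthwhile but smaller point about efficiency and pre-specification. If the strata are omitted, the tests are conservative and less powerful, and the arm effect remains unbiased. The size rests on an R² that the article does not supply: intervals 3–8% wider if the strata explain a further 5–15% of variance after baseline, and negligible if they explain almost none.

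A reader might extend the loss of precision to the 12 inflammatory markers and the CpG sites. That does not follow: stratum main effects have essentially no influence on the group-by-time test, and adding the baseline value there would put it on both sides of a model that already treats baseline as an outcome.

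**What to change.** 1. State contiguous BMI strata that cover every eligible BMI, for example 18.5–24.9, 25–29.9 and 30+.
2. Check that the REDCap allocation table matches. If it has a middle category, correct the text only; if it does not, report how women with BMI 25–29.9 were allocated.
3. In the 20-week and 1-year linear models for weight, waist and fruit and vegetable intake, name BMI category and race/ethnicity as covariates alongside the baseline value of the outcome.
4. Limit any further covariates in those primary models to variables measured before randomisation.
5. Leave the marker mixed model as it is on this point.

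The cost is a wording correction, one check of the allocation table and a few degrees of freedom: five if the two factors enter as main effects (2 for BMI category, 3 for race/ethnicity), or 12 − 1 = 11 if every cell has its own term, with 400 women.

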### Fruit and vegetable intervention arm

During the first 20 weeks of the intervention, participants will receive weekly produce boxes providing 32 servings of fruits and vegetables. The boxes will be comprised of 75% vegetables, with at least six servings of leafy greens. To encourage intake of variety of fruits and vegetables, a packing guide for produce boxes will be created based on nutrients and phytochemicals groupings developed by and Fisher (Table 1) [20]. At least one item from each category will be packed into the supplemental box of produce, which will be delivered to each participant along with recipes to assist in meal preparation. These boxes of fruits and vegetables will assist participants to transition from their pre-study diet and are intended to help the intervention participants achieve their goal of consuming 8 to 10 servings of fruits and vegetables, but not to supply their total fruit and vegetable intake or to restrict other produce intake. The produce box will contain a combination of fresh and frozen fruits and vegetables, providing participants with food preparation options. Participants will not be deterred from consuming canned produce, since research indicates canned and frozen fruits and vegetables are nutritionally sound alternatives to fresh produce [21–23]. The content of weekly boxes will be modified based on availability and study participant allergies.

**Table 1 Tab1:** Study activities at each assessment

	Pre-enrollment	Baseline	10 weeks	20 weeks	1 year
*Eligibility*					
Informed consent	X				
Eligibility Screener	X				
Fruit and vegetable screener	X				
*Randomization*					
Randomization		X			
Nutrition education session		X			
*Intervention arm only*					
Fruit and vegetable delivery (weekly for 20 weeks)		X	X	X	
Dietary counseling (weekly for 20 weeks then monthly up to 1 year)		X	X	X	
Three 24-Hour Diet Records (weekly for 20 weeks to guide counseling)		X	X	X	
Monthly counseling check-ins (between 20 weeks and one year)				X	X
*Anthropometrics*					
Maternal height	X	X			
Maternal weight	X	X	X	X	X
Maternal waist circumference		X	X	X	X
Infant length and weight		X	X	X	X
*Biological sample collection*					
Breastmilk specimen (if still breastfeeding)		X	X	X	X
Infant fecal specimen		X	X	X	X
Maternal fecal specimen (optional)		X		X	X
*Questionnaire data*					
Three 24 hour diet recalls (ASA24)		X	X	X	X
Breastfeeding Practices Questionnaire		X			
Breastfeeding Update Questionnaire			X	X	X
New Moms Health Questionnaire		X			
Medication and Supplement Questionnaire		X	X	X	X
Infant and Child Feeding Questionnaire		X	X	X	X
Physical Activity Questionnaire (IPAQ)		X	X	X	X
Breast Health Questionnaire					X

The dietary intervention group will also receive weekly tailored counseling over the phone to promote intake of 8–10 daily servings of fruits and vegetables. Nutrition counseling and support will occur on a weekly basis from six weeks postpartum until 26 weeks postpartum, when the supplemental produce boxes will be discontinued. At this point, nutrition counseling will continue, with less frequency, up to the end of the 12-month intervention. Individualized counselling will involve supportive and motivational interviewing and goal setting techniques to help participants achieve intervention goals (e.g., modifying recipes and food preparation) [24, 25]. Servings are defined as 1 cup of cut, raw or cooked vegetables or fruit, or two cups of raw leafy vegetables. Fruit juices are not counted toward daily goals, because of their association with weight gain [26] and due to the removal of key nutrients such as fiber.

Participants will monitor their compliance to the intervention by keeping three food records per week (two weekdays and one weekend) and recording, in as much detail as possible, all food, beverages, and supplements consumed in 24 h. These daily records will be collected weekly (for the first 20 weeks), reviewed by the nutrition counselors and used to monitor participant progress. Recording their own intake will also help participants focus on their food choices so they can find ways to increase their fruits and vegetables without disrupting their daily routine. After 20 weeks, the weekly counseling will be guided by a series of questions related to maintaining the study goal of consuming 8 to 10 daily servings of fruits and vegetables per day.

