#### Inflammatory markers

We will use Mesoscale Discovery electrochemiluminescent sandwich assays to determine concentrations of 12 inflammatory markers in bilateral breastmilk samples collected at baseline and 20 weeks (adiponectin, leptin, c-reactive protein (CRP), interferon-γ (IFN-γ), interleukin-1β (IL-1β), interleukin-6 (IL-6), interleukin-8 (IL-8), tumor necrosis factor-α (TNF-α), basic fibroblast growth factor (bFGF), fms related receptor tyrosine kinase 1 (FLT1), placental growth factor (PlGF), vascular endothelial growth factor-D (VEGF-D) as described in a previous study [28].

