### Power and sample size calculations

Power calculations for linear mixed models with adjustment for multiple testing were carried out through simulation studies. Due to computational considerations, adjustment for multiple testing was carried out through a conservative Bonferroni correction procedure to maintain the overall type I error at 0.05. CpG measurements (1a): In each dataset, we simulated repeated measurements of CpG levels according to a multivariate normal distribution with unit variance, assuming a within-subject correlation ρ, a mean difference in levels in the *control group* comparing baseline to the 20-week (T2) visit equal to 0.1 SD units and a mean difference in the intervention group between the 20-week (T2) and baseline (T0) of Δ SD units. The threshold for statistical significance was set at p = 0.05/300000, corresponding to a Bonferroni correction to maintain the overall Type I error at 0.05. When the correlation between the repeated CpG measurements is set to ρ = 0.5 (ρ = 0.3), a sample size of 200 per group results in 99% (82%) power to detect a mean difference in the intervention arm between baseline and T2 of Δ = 0.75 SD units, obtained by averaging over 100 simulated datasets. For the analysis of the 12 inflammatory markers, we simulated repeated measurements of inflammatory marker levels according to a multivariate normal distribution as described above. Assuming a Bonferroni correction to maintain the overall Type I error at 0.05 and when the correlation between the repeated inflammatory measurements is set to ρ = 0.5 (ρ = 0.3), a sample size of 200 per group results in 94% (84%) power to detect a mean difference in the intervention arm between baseline and T2 of Δ = 0.45 SD units, obtained by averaging over 100 simulated datasets.

Power calculations for the analyses of body weight, waist circumference and fruit and vegetable consumption at 1 year were based on a generalized linear model, using the R package pwr [32]. A sample size of 400 subjects results in 98% power to detect an effect size of 0.05 or larger, assuming a two-sided test and a type I error 0.05. We assumed the same variability at the two time points so the power is the same for 20 weeks and one year.

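### The stated biomarker power is an upper bound: it needs a 20-week milk sample from every randomised woman, but milk is collected only from women still breastfeeding

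*Protocol article*

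**What the plan says.** **Number randomised.** The Overview in the protocol article says "Eligible women will be enrolled at five to six weeks postpartum and randomly assigned" and sets the arms at "target n = 200) or to Control Arm (target n = 200". The 200 is thus counted at randomisation, not at 20 weeks.

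**Number in the power calculation.** Under Power and sample size calculations, the CpG simulation reports that "a sample size of 200 per group results in 99% (82%) power" and the inflammatory-marker simulation that "a sample size of 200 per group results in 94% (84%) power". The first figure is for a within-subject correlation of 0.5, the bracketed one for 0.3.

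**Samples needed.** The Inflammatory markers section measures the 12 markers "in bilateral breastmilk samples collected at baseline and 20 weeks". The DNA methylation section uses the same two time points, and the Data analysis section tests group by time on those two measurements in a random-intercept model.

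**Who can give the sample.** Table 1 lists the milk collection as "Breastmilk specimen (if still breastfeeding". Baseline is at about six weeks postpartum, so the 20-week visit falls at about 26 weeks postpartum.

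**One year.** For weight, waist and fruit and vegetable intake the power section says: "We assumed the same variability at the two time points so the power is the same for 20 weeks and one year".

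**The concern.** The schedule foresees that some women will have no milk to give at 20 weeks. The power calculation counts every randomised woman as giving it. A woman who weans or leaves before the 20-week visit contributes no follow-up value for methylation or inflammation, and the article contains no inflation factor, expected weaning rate or dropout rate.

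The stakes lie in how a negative result is read. If no CpG site or marker passes its threshold, readers will judge that against a claimed power of 82% to 99%. If a sizeable share of 20-week samples is missing, the actual power is lower. The CpG endpoint is the most exposed, because its threshold of 0.05/300,000 makes power fall quickly as the standard error grows.

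**Working it through.** **Inputs from the article**
- 200 per arm, 1:1 allocation (Overview; Randomization).
- Unit variance, ρ = 0.5 or 0.3, effect Δ = 0.75 SD (CpG) or 0.45 SD (inflammatory), Bonferroni thresholds, 100 simulated datasets (Power and sample size calculations).
- Random-intercept mixed model, likelihood ratio test of group by time on baseline and 20 weeks (Data analysis). Table 2 also marks 10 weeks, but the model and the simulations use two time points, so the check does too.

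**Assumptions**
- Δ is the net difference in change between the arms.
- Loss of the 20-week sample is equal in both arms and random. The rate is not given; 0% to 40% is shown.

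**Step 1: reproduce the stated power with no loss.** With n = 200 complete pairs per arm, SE = √(2 × 2(1−ρ)/n) and power = Φ(Δ/SE − z).
- z = 5.233 for α = 0.05/300,000 and z = 2.865 for α = 0.05/12, both two-sided.
- SE = 0.1000 at ρ = 0.5 and 0.1183 at ρ = 0.3.
- CpG, ρ = 0.5: Φ(7.500 − 5.233) = 98.8% (stated 99%).
- CpG, ρ = 0.3: Φ(6.339 − 5.233) = 86.6% (stated 82%).
- Inflammatory, ρ = 0.5: Φ(4.500 − 2.865) = 94.9% (stated 94%).
- Inflammatory, ρ = 0.3: Φ(3.803 − 2.865) = 82.6% (stated 84%).

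A 20,000-run simulation of the likelihood ratio test gives 98.5%, 84.6%, 94.4% and 82.2%. With 100 datasets, a stated 82% has a Monte Carlo standard error of √(0.82 × 0.18/100) = 3.8 points, which covers the one visible gap. The stated figures are therefore those for 200 complete pairs per arm, with no loss built in.

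**Step 2: power with loss, under the planned model.** Let m be the number per arm with both samples. The mixed model also uses the 200 − m women with baseline only, so the variance of one arm's mean change is (1−ρ²)/m + (1−ρ)²/200, and SE = √(2 × that variance). At m = 200 this reduces to Step 1.

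Example, CpG, ρ = 0.3, 20% loss (m = 160): variance = 0.91/160 + 0.49/200 = 0.00569 + 0.00245 = 0.00814; SE = √0.01628 = 0.1276; power = Φ(0.75/0.1276 − 5.233) = Φ(5.879 − 5.233) = 74.1%.

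| 20-week samples lost (m per arm) | CpG ρ=0.5 | CpG ρ=0.3 | Inflammatory ρ=0.5 | Inflammatory ρ=0.3 |
|---|---|---|---|---|
| 0% (200) | 98.8 | 86.6 | 94.9 | 82.6 |
| 10% (180) | 97.6 | 81.3 | 92.8 | 79.0 |
| 20% (160) | 95.0 | 74.1 | 89.7 | 74.6 |
| 30% (140) | 90.2 | 64.5 | 85.3 | 69.1 |
| 40% (120) | 81.3 | 52.4 | 79.1 | 62.2 |

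Read down each column, so that formula is compared with formula. The drop at 10% loss is 1.2, 5.3, 2.1 and 3.6 points; at 20% it is 3.8, 12.5, 5.2 and 8.0 points.

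**Step 3: why complete pairs alone would exaggerate.** Dropping baseline-only women changes the SE to √(4(1−ρ)/m). CpG power at ρ = 0.3 then reads 66.9%, 52.8% and 37.3% at 20%, 30% and 40% loss, up to 15 points below the table. That is not the planned analysis.

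**Step 4: one year.** The article does not define its effect size of 0.05. If it is f² in a linear model (an assumption), power at n = 400 is 99.4% with one numerator degree of freedom and 98.5% with two. With 20% dropout (n = 320) it is 97.9% or 95.5%.

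**The case against.** A reader might infer that the design cannot deliver its stated power. The documents do not support that. They give no loss rate, and at 10% loss the planned model stays within about 5 points of its own no-loss value, which is hard to separate from the error of 100 simulations. What they support is that the stated figures are a ceiling.

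A reader might also take the shortfall from complete pairs only. Step 3 shows that this overstates it, because the mixed model retains women with a baseline sample.

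Three defences of the plan deserve an answer.
- *The article condenses a fuller protocol, which may hold a retention assumption.* It may. But the article prints the same 200 as randomisation target and as power sample size, beside a schedule that makes the sample conditional. The issue is a stated result that does not match its own design.
- *All women have access to a lactation counselor, and imputation will be considered.* Counselling may reduce weaning but does not justify assuming none. Imputation is offered as a robustness check and creates no milk data.
- *Bonferroni is conservative, so there is reserve.* The planned Benjamini-Yekutieli procedure divides by a further 3.10 for 12 tests and 13.2 for 300,000. With few non-null markers it is stricter than Bonferroni, so the reserve is not assured.

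The 1-year statement is a weaker matter. Weight, waist and diet do not require breastfeeding, so only ordinary dropout applies, and on the reading in Step 4 its effect is small.

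**Conclusion.** The concern holds in this form: the biomarker power of 99%/82% and 94%/84% requires all 200 randomised women per arm to give milk at both visits, so the figures are upper bounds with no allowance for weaning or dropout. Nothing is miscalculated at n = 200; the fault is an unstated assumption that Table 1 itself makes doubtful.

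The shortfall is small at about 10% loss and becomes material from about 20%, above all at ρ = 0.3, where both endpoints are then near 75%. At ρ = 0.5, CpG power stays above 80% even at 40% loss, and inflammatory-marker power is then 79%.

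The direction is certain. The size rests on the assumed loss rate, on loss being random and equal between arms, on Bonferroni thresholds, and on Δ being the net difference. If the article's wording is taken literally (control change 0.1 SD, intervention change Δ), the net effects are 0.65 and 0.35 SD and power with no loss is already 89.7% (60.3%) for CpG and 73.7% (53.7%) for inflammatory markers. That is a separate question, but loss would lower those values further.

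**What to change.** In Power and sample size calculations, restate biomarker power for the expected number of women with a 20-week milk sample. Use the planned mixed model, give the assumed loss rate with its basis, and show a range such as 0% to 40% at both correlations. Describe the present figures as the no-loss case.

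In a separate sentence, state the retention assumed for weight, waist and fruit and vegetable intake at 20 weeks and at one year, since equal variability alone does not make power equal at the two times.

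The cost is a few lines and one small table, plus less favourable figures. No extra enrolment and no change to study procedures are needed.
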